#### 2.6.2. Secondary Outcome Measures

Secondary outcome measurements will be the changes from baseline (T0) to post-treatment (T1) and follow-up assessment (T2) in standardized clinical, communication, and functional abilities questionnaires, as well as neuropsychological tests for each cognitive domain and specific language task. 

In particular, we will compute changes in clinical, communication, and functional abilities: Stroke and Aphasia Quality of Life Scale—39 (SAQoL—39 [47]): measures the health-related quality of life in people with chronic aphasia. It provides a total score from 1 to 5 (higher score = better outcome), and it analyzes the following four domains: physical (score range: min = 1, max = 5; higher score = better outcome); psychosocial (score range: min = 1, max = 5; higher score = better outcome); communication (score range: min = 1, max = 5; higher score = better outcome), and energy (score range: min = 1, max = 5; higher score = better outcome);Communication Outcome After Stroke (COAST [48]): a measure of functional communication in daily activities and of its impact on the quality of life from the point of view of the aphasia patient (COAST total score range: min = 0, max = 80; higher score = better outcome) and their carer (Carer COAST total score range: min = 0, max = 80; higher score = better outcome);Functional Outcome Questionnaire-aphasia [49]: measures an aphasia patient’s functional and pragmatic communication in the home and community settings. It provides a total score from 32 to 160 (higher score = better outcome), and it is divided into four subscales: communicating basic needs (CBN score range: min = 1, max = 35; higher score = better outcome); making routine requests (MRR score range: min = 1, max = 35; higher score = better outcome); communicating new information (CNI score range: min = 1, max = 40; higher score = better outcome), and attention/other communication skills (AO score range: min = 1, max = 50; higher score = better outcome);Frontotemporal Dementia—Clinical Dementia Rating Scale (FTD-CDR)—Sum of Boxes [50]: a measure of dementia severity and progression in FTD (score range: min = 0, max = 24; higher score = worse outcome);Global Clinical Dementia Rating (CDR) plus NACC FTLD [51]: a measure of dementia severity and progression in FTD (score range: min = 0, max = 3; higher score = worse outcome);Progressive Aphasia Severity Scale (PASS [34,35]): measures the severity and progression of language deficits in patients with PPA. The scale assesses ten linguistic domains (each score range: min = 0, max = 3): articulation (higher score = worse outcome), fluency (higher score = worse outcome), syntax and grammar (higher score = worse outcome), word retrieval and expression (higher score = worse outcome), repetition (higher score = worse outcome), auditory comprehension (higher score = worse outcome), single-word comprehension (higher score = worse outcome), reading (higher score = worse outcome), writing (higher score = worse outcome), and functional communication (higher score = worse outcome). Moreover, it analyzes three supplemental domains (each score range: min = 0, max = 3): initiation of conversation (higher score = worse outcome), turn-taking during conversation (higher score = worse outcome), and generation of language (higher score = worse outcome);Lincoln Speech Questionnaire [52]: measures functional communication skills. It provides a speech score (score range: min = 0, max = 14; higher score = better outcome) and an understanding score (score range: min = 0, max = 5; higher score = better outcome);Communication Severity Rating Scale (Goodglass and Kaplan [53]): a measure of aphasia severity (score range: min = 0, max = 5; higher score = better outcome);Beck Depression Inventory (BDI [54]): a measure of depressive symptoms (score range: min = 0, max = 63; higher score = worse outcome);Frontal Behavioral Inventory (FBI [55]): a measure of behavior and personality (score range: min = 0, max = 72; higher score = worse outcome).

Moreover, the neuropsychological battery will include tests for the assessment of global cognition (Mini Mental State Examination, MMSE [56,57]; score range: min = 0, max = 30; higher score = better outcome) and for the deep evaluation of the following domains:

##### Language

Picture Naming subtest from Screening for Aphasia in NeuroDegeneration (SAND [58,59]): a measure of naming abilities. It provides a total score (score range: min = 0, max = 14; higher score = better outcome), a living score (score range: min = 0, max = 7; higher score = better outcome), and a non-living score (score range: min = 0, max = 7; higher score = better outcome);Auditory sentence comprehension subtest from Screening for Aphasia in NeuroDegeneration (SAND [58,59]): a measure of comprehension abilities (total score range: min = 0, max = 8; higher score = better outcome);Single-word comprehension subtest from Screening for Aphasia in NeuroDegeneration (SAND [58,59]): a measure of comprehension abilities. It provides a total score (score range: min = 0, max = 12; higher score = better outcome), a living score (score range: min = 0, max = 6; higher score = better outcome), and a non-living score (score range: min = 0, max = 6; higher score = better outcome);Repetition subtest from Screening for Aphasia in NeuroDegeneration (SAND [58,59]): a measure of repetition abilities. It provides a total score (score range: min = 0, max = 10; higher score = better outcome), a words score (score range: min = 0, max = 6; higher score = better outcome), and a non-words score (score range: min = 0, max = 4; higher score = better outcome);Sentence repetition subtest from Screening for Aphasia in NeuroDegeneration (SAND [58,59]): a measure of repetition abilities. It provides a total score (score range: min = 0, max = 6; higher score = better outcome), a predictable sentences score (score range: min = 0, max = 3; higher score = better outcome), and an unpredictable sentences score (score range: min = 0, max= 3, higher score = better outcome);Reading subtest from Screening for Aphasia in NeuroDegeneration (SAND [58,59]): a measure of reading abilities. It provides a total score (score range: min = 0, max = 16; higher score = better outcome), a words score (score range: min = 0, max= 12; higher score = better outcome), and a non-words score (score range: min = 0, max = 4; higher score = better outcome);Writing subtest from Screening for Aphasia in NeuroDegeneration (SAND [58,59]): a measure of writing abilities. It provides an Information Units score (score range: min = 0, max = 6; higher score = better outcome), a total number of words score (score range: min = 0, max = no limits; higher score = better outcome), a number of nouns/total number of words score (score range: min = 0, max = 1; higher score = better outcome), a number of verbs/total number of words (score range: min = 0, max = 1; higher score = better outcome), a number of correct syntactic structures/total number of syntactic structures score (score range: min = 0, max = 1; higher score = better outcome), a number of orthographic errors score (score range: min = 0, max = no limits; higher score = worse outcome), and a number of lexico-semantic errors/number of words score (score range: min = 0, max = 1; higher score = worse outcome);Semantic association subtest from Screening for Aphasia in NeuroDegeneration (SAND [58,59]): a measure of semantics (total score range: min = 0, max = 4; higher score = better outcome);Picture description subtest from Screening for Aphasia in NeuroDegeneration (SAND [58,59]): a measure of oral production. It provides an Information Units score (score range: min = 0, max = 8; higher score = better outcome), a total number of words score (score range: min = 0, max = no limits; higher score = better outcome), a number of nouns/total number of words score (score range: min = 0, max = 1; higher score = better outcome), a number of verbs/total number of words score (score range: min = 0, max = 1; higher score = better outcome), a number of sentences score (score range: min = 0, max = no limits; higher score = better outcome), a number of subordinates/number of sentences score (score range: min = 0, max = no limits; higher score = better outcome), a number of repaired sequences/number of words score (score range: min = 0, max = 1; higher score = worse outcome), a number of phonological errors/number of words (score range: min = 0, max = 1; higher score = worse outcome), and a number of lexico-semantic errors/number of words (score range: min = 0, max = 1; higher score = worse outcome);Naming Subtest from the Aachener Aphasia Test [60]: a measure of oral naming (score range: min = 0, max = 120; higher score = better outcome);Object naming subtest from Battery for the Assessment of Aphasic Disorders (BADA [61]): a measure of object naming (score range: min = 0, max = 30; higher score = better outcome);Verbal Fluency (semantic and phonemic [62]): a measure of verbal fluency abilities (score range min = 0, max = no limits; higher score = better outcome).

##### Memory

Story Recall [63]: a measure of verbal long-term memory (score range min = 0, max = 28; higher score = better outcome);Rey-Osterrieth Complex Figure—Recall [64]: a measure of nonverbal long-term memory (score range min = 0, max = 36; higher score = better outcome).

##### Attention and Executive Functions

Trial Making Test [65]: a measure of attentional abilities (score range: min = n/a, max = no limits; higher score = worse outcome);Stroop Test [66]: a measure of executive abilities (score range: min = n/a, max = no limits; higher score = worse outcome).

##### Constructional Praxis

Rey-Osterrieth Complex Figure—Copy [64]: a measure of constructional praxis (score range min = 0, max = 36; higher score = better outcome).

#### 2.6.3. Surrogate Outcome Markers

Surrogate outcome measures will be the changes from baseline (T0) to post-treatment (T1) in molecular biomarkers and structural and functional connectivity. 

In plasma, we will analyze the following: The size and the concentration of plasma extracellular vesicles (EVs) by nanoparticle tracking analysis, employing the Nano-Sigh Instrument (Malvern, Worcestershire, United Kingdom);Neurofilament light chain (NFL) levels and Glial Fibrillary Acidic Protein (GFAP) levels using the commercially available Neurology 2-Plex B array (Quanterix, Lexington, MA) on the automated Simoa® SR-X analyzer (Quanterix);Brain-derived neurotrophic factor (BDNF) and Neurogranin levels by using commercially available arrays, employing the Bio-Plex 200 System array reader (Bio-Rad, Hercules, CA, USA).

Biological samples will be stored in the BioBank of the IRCCS Istituto Centro San Giovanni di Dio, Fatebenefratelli.

Structural and functional connectivity will be measured using the following: Resting-state functional magnetic resonance imaging (MRI) to derive functional connectivity matrices;Diffusion-weighted MRI to derive structural connectivity matrices.

In detail, a high-field 3T scanner will be used, and an MRI connectivity study on brain networks mediating language will be adopted. Imaging analysis will be conducted by using a combination of neuroimaging software (Statistical Parametric Mapping (SPM12, http://www.fil.ion.ucl.ac.uk/spm/ (accessed on 6 July 2023)); FSL (https://fsl.fmrib.ox.ac.uk/fsl/fslwiki (accessed on 6 July 2023)), GIFT (http://mialab.mrn.org/software/gift/ (accessed on 6 July 2023)), and FreeSurfer (https://surfer.nmr.mgh.harvard.edu/ (accessed on 6 July 2023)).

### 2.7. Data Collection

Demographic characteristics will be collected at the baseline evaluation (T0). Likewise, screening tools for handedness (Edinburgh Handedness Inventory (EHI, [67]), screening checklist for the application of tDCS, and Cognitive Reserve Index questionnaire (CRI-q, [68]) will be administered at the baseline assessment (T0). Data from clinical, cognitive, and language measures (primary and secondary outcomes) will be collected at the baseline (T0) and at each timepoint of evaluation (T1 and T2). MRI and biomolecular data will be collected only at T0 and T1. Primary and secondary outcome measures will be assessed for a single patient by the same trained neuropsychologist (blinded to patient treatment allocations) for all visits.

Moreover, at the end of each tDCS session, all participants will be asked to complete questionnaires to assess any adverse events and sensations induced by the tDCS [69]. After completing the last treatment session, participants will be asked whether they believe they received the active or sham stimulation (dichotomous response).

### 2.8. Statistical Analysis

A repeated-measures analysis will be used to compare pre-treatment (T0) versus post-treatment (T1) and follow-up (T2) variables for the two groups. Regarding MRI, the data will be analyzed using repeated-measures ANOVAs by testing different experimental factors: timing (T0, T1), hemisphere, and electrode site. Correlations between cognitive/functional changes, imaging biomarkers, and molecular biomarkers will be assessed by using Pearson’s correlation coefficient.

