### 2.1. Trial Design and Setting

This multicentric study is a double-blinded, randomized, controlled pilot study involving 60 patients with mild PPA, defined using the Progressive Aphasia Severity Scale (PASS) [34,35], recruited from IRCCS Istituto Centro San Giovanni di Dio, Fatebenefratelli, Brescia; IRCCS Fondazione Mondino, Pavia; Fondazione IRCCS Ca’ Granda Ospedale Maggiore Policlinico, Milan, and Fondazione Don Carlo Gnocchi—ONLUS, Milan, Italy.

After recruitment, the subjects will be randomized into one of two parallel groups: (i) active tDCS over the DLPFC combined with an individualized language training group or (ii) placebo DLPFC-tDCS with an individualized language training group. The two groups will be matched for age, education, and language deficit severity. All participants will undergo a clinical, cognitive, and language evaluation at the baseline (T0), post-treatment (T1), and at the 3-month (T2) follow-up. Magnetic Resonance Imaging (MRI) and biomolecular data will be collected at T0 and T1 (after the treatment). The trial work plan is shown in Figure 2.

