### 2.2. Sample Size

The sample size calculation was computed using G*Power 3 software [36,37]. The sample size for this pilot study was determined based on previous work [38] and was computed for the primary outcome variable (an increase in naming accuracy). An eta square of 0.25 of the interaction between time and the experimental group was considered for the effect size calculation. A minimum sample size of 12 subjects is required for a 90% powered study (alpha = 0.05). The resulting number was increased to 30 subjects per group based on the 20% expected dropout rate among the subjects and because of the considerable individual variability expected from the inclusion of all PPA variants.

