### 2.3. Study Population, Recruitment, and Randomization

According to the sample size calculation, the MAINSTREAM trial has a target enrollment of 60 patients diagnosed with mild PPA, defined using the Progressive Aphasia Severity Scale (PASS) [34,35]. Eligible patients who meet all inclusion criteria (see the paragraph below) will be randomized using an adaptive randomization procedure. Clinicians and patients will be blinded to the trial intervention. The group allocation will be masked to the statistician conducting the data analysis.

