### 2.6. Outcome Measures

#### 2.6.1. Primary Outcome Measures

The primary outcome measure will be the change from baseline (T0) to post-treatment (T1) and follow-up assessment (T2) in object- and action-naming task scores, as assessed by the International Picture Naming Project (IPNP) Task [46]. 

At the baseline assessment (T0), the patients will undergo two sessions of oral object naming to select object stimuli for the treatment (trained items) and control object stimuli for the assessment of generalization effects (untrained items). Pictures for the oral naming task will include 300 black-and-white drawings of objects taken from the UCSD Center for Research in Language—International Picture-Naming Project corpus [46]. This database provides norms and lexical information (frequency, age of acquisition, etc.) for picture naming in seven languages. The pictures have been tested and normed on healthy and patient populations [46]. In this protocol, the pictures for the oral naming task will be displayed twice (on two consecutive days) on a computer screen using Microsoft PowerPoint; each picture will be presented for a maximum of 6 s. Each participant will be asked to name the object, and oral responses will be recorded.

The pictures not correctly named by the participant in at least one out of the two oral naming sessions will be further split into two sets: the “therapy” list, which will include the items to be trained (trained stimuli), and the control stimuli list, which will include items not to be trained (untrained stimuli). The two lists will be balanced as closely as possible for several variables (e.g., word frequency, number of syllables, semantic category, etc.). The procedure that will be applied to select the “therapy” and “control” lists will produce a personalized set of items for each participant, which ensures the within- and across-subject validity of the design. The accuracy in naming trained and untrained items will be assessed at the end of the rehabilitation (T1) and during follow-up visits (T2). 

Moreover, naming oral action items will be evaluated to assess generalization effects. 

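### The planned group comparison is a change-from-T0 contrast, with no adjustment named for baseline naming or for the matched factors, which may cost precision

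*Protocol article*

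**What the plan says.** Section 2.8 (Statistical Analysis) states: "A repeated-measures analysis will be used to compare pre-treatment (T0) versus post-treatment (T1) and follow-up (T2) variables for the two groups". It names no covariate. Repeated-measures ANOVA is named only in the next sentence, for MRI.

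Two other sections fix the role of T0:
- Section 2.6.1 (Primary Outcome Measures): "The primary outcome measure will be the change from baseline (T0) to post-treatment (T1) and follow-up assessment (T2") in the object- and action-naming scores.
- Section 2.2 (Sample Size): "An eta square of 0.25 of the interaction between time and the experimental group was considered for the effect size calculation".

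On allocation, Section 2.1 says "The two groups will be matched for age, education, and language deficit severity", and Section 2.3 says eligible patients "will be randomized using an adaptive randomization procedure". No section says whether age, education or severity enter the analysis. Section 1.2 sets out to evaluate both short-term and long-term effects.

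**The concern.** When T0 is one of the repeated responses and the test is time by group, the arms are compared on change from T0. That forces the slope of follow-up on baseline to be 1. Adjusting for T0 estimates the slope instead, and in a randomised trial this gives a group contrast that is at least as precise.

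A second loss is possible. If allocation balances the arms on factors that predict the outcome being compared, and the model omits those factors, the standard error still counts variation that the design has removed. Intervals are then wider than they need to be and cover too often.

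At stake is information in a small trial. The plan has 60 patients, and with a "20% expected dropout rate among the subjects" about 60 × 0.8 = 48 would complete. Section 2.2 itself expects large individual variability because all PPA variants are enrolled. A comparison across three visits also does not by itself give the separate short-term and long-term answers that Section 1.2 seeks.

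**Working it through.** **1. The plan's own figure.** Section 2.2 says: "A minimum sample size of 12 subjects is required for a 90% powered study (alpha = 0.05"). An eta squared of 0.25 gives f² = 0.25/0.75 = 0.333 (f = 0.577). For a within-between interaction with two groups and m visits, lambda = f²·N·m/(1−rho), df1 = m−1 and df2 = (N−2)(m−1). The article gives no rho or sphericity value, so rho = 0.5 and epsilon = 1 are assumed.
- Two visits, N = 12 in total: lambda = 0.333 × 12 × 2/0.5 = 16, power 0.949. N = 10 gives 0.891, so 12 is the smallest even total.
- Three visits, same convention: N = 10 gives 0.961.
- Three visits, with 0.25 taken as a partial eta squared (lambda = f²(N−2)(m−1)): 24 in total, or 12 per group, gives 0.922.

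The 12 is thus reproduced as a total under one plausible set of inputs. None of these calculations contains a covariate, which fits the reading of Section 2.8 as an unadjusted time by group comparison.

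**2. Baseline as response or as covariate.** Let s0 and s1 be the SDs at T0 and follow-up, and rho their correlation. Per patient:
- change: s0² + s1² − 2·rho·s0·s1
- adjusted for T0: s1²(1 − rho²)
- difference: (s0 − rho·s1)², which is never negative and is zero when s0 = rho·s1.

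With s0 = s1 the ratio of adjusted to change variance is (1−rho²)/(2(1−rho)) = (1+rho)/2. The article gives no rho, so a range is shown:

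| rho | variance ratio | interval narrower by | patients giving the precision of 48 |
|---|---|---|---|
| 0.3 | 0.65 | 19% | 31 |
| 0.5 | 0.75 | 13% | 36 |
| 0.7 | 0.85 | 8% | 41 |
| 0.8 | 0.90 | 5% | 43 |
| 0.9 | 0.95 | 2.5% | 46 |

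The third column is 1 − √ratio and the fourth is 48 × ratio.

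**3. Effect of item selection.** Section 2.6.1 draws the trained and untrained lists from pictures failed at least once at T0. This restricts s0 and probably rho as well. With k = s0/s1 the ratio is (1−rho²)/(1 + k² − 2·rho·k):
- rho 0.3, k 0.6: 0.91/1.00 = 0.91
- rho 0.3, k 0.4: 0.91/0.92 = 0.99
- rho 0.5, k 0.6: 0.75/0.76 = 0.99
- rho 0.5, k 0.4: 0.75/0.76 = 0.99

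On these lists the gain from the baseline score may be almost nothing.

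**4. Matched factors left out.** If they explain a share R² of the variance of change and are well balanced, the unadjusted interval is 1/√(1−R²) times the adjusted one: 1.05, 1.12 and 1.20 at R² of 0.1, 0.2 and 0.3. The article gives no R². A factor that shifts naming equally at T0 and follow-up has R² = 0 for change and costs nothing here.

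**The case against.** The article condenses a fuller plan. Section 2.8 does not exclude covariates, and a covariate list may sit in an analysis plan that is not shown. The phrase used could also cover a mixed model with a common baseline mean, which is about as efficient as baseline adjustment. Section 2.3 does not name the factors used by the adaptive procedure, so the link to the matching in Section 2.1 is an inference. All of this stands, and the point is therefore that the article names no adjustment, not that it rules one out. What is stated is the role of T0: three sections agree that the contrast is change from baseline.

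Three stronger readings are tempting and not supported.

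- *A reader might infer that the test's error rate is far below 5% and that much power is lost.* That holds for a single-visit comparison that omits a balanced factor. In a simulation with 48 patients, one perfectly balanced binary factor acting equally at both visits, and a T0–T1 correlation of 0.5, the post-only test rejected in 2.7%, 2.0% and 1.1% of null trials at R² of 0.2, 0.3 and 0.4. The change test on the same data stayed at about 5%, because the factor cancels.
- *A reader might infer that patients without T2 are deleted and the contrast biased.* This needs a classical ANOVA, which Section 2.8 names only for MRI. A likelihood-based model keeps their T1 data.
- *A reader might infer that the truncated T0 score makes baseline adjustment especially valuable.* Step 3 of the working points the other way.

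**Conclusion.** The point holds as one of efficiency. As described, the primary comparison is a change contrast with no named adjustment, and under a linear model it cannot be more precise than a baseline-adjusted one.

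The size cannot be fixed from the article. With equal SDs, adjustment would narrow intervals by 2.5% to 19% for rho from 0.9 to 0.3. On the item lists selected at T0 the gain may be near zero. Omitting the matched factors would widen intervals by about 5% to 20% only if they explain 10% to 30% of the variance of change and the allocation does balance them.

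The loss is precision, not bias, and the documents do not show a distorted error rate. The change is still worth making: the trial is small, its population is heterogeneous, and the improvement is nearly free.

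**What to change.** Replace the sentence in Section 2.8 with a likelihood-based mixed model for naming accuracy at T1 and T2, using all available post-baseline data. Include:
- group, visit, and group by visit;
- baseline naming score by visit;
- age, education and language severity as covariates.

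A model that keeps T0 as a response but constrains the two groups to a common baseline mean is an acceptable alternative, with the same three covariates. Report separate group contrasts at T1 and T2, to answer the short-term and long-term aims in Section 1.2.

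The cost is analysis wording and a few degrees of freedom: if each term is linear, one each for baseline, baseline by visit, age, education and severity, so 5 in all. The covariates are already used for matching or measured at T0. No extra patients or visits are needed.

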### 1.2. Objectives

In this double-blind, randomized, controlled pilot study, we aim to test tDCS neuromodulation coupled with language therapy in rehabilitation settings. In particular, we will evaluate the short-term and long-term effects of active tDCS over the dorsolateral prefrontal cortex (DLPFC) combined with individualized language training vs. placebo DLPFC-tDCS with individualized language training in a large sample of patients with mild PPA. In particular, we aim to establish if the combined use of active tDCS and individualized language training in mild PPA patients can improve cognitive and functional performance. Moreover, we aim to evaluate the changes in brain activity and molecular markers as they relate to the intervention. To date, little is known about the mechanisms of the treatment’s effects. This trial could partially fulfil the need for new rehabilitation instruments to be used in daily disease management. It will increase understanding of the neural and biological characteristics linked to the effect of language treatment and non-invasive brain stimulation application in PPA.

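### Plain Pearson correlations between outcome changes and markers carry no arm term; if the arms are pooled, a shared response to treatment can pass for a patient-level link

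*Protocol article*

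**What the plan says.** Section 2.8 (Statistical Analysis) gives one sentence on association: "Correlations between cognitive/functional changes, imaging biomarkers, and molecular biomarkers will be assessed by using" Pearson's correlation coefficient. It mentions no arm term, no partial correlation and no within-arm analysis, and it does not say that the arms are pooled.

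The markers are defined in Section 2.6.3: "Surrogate outcome measures will be the changes from baseline (T0) to post-treatment (T1) in molecular biomarkers and structural and functional connectivity". The plasma list covers "The size and the concentration of plasma extracellular vesicles (EVs) by nanoparticle tracking analysis", "Neurofilament light chain (NFL) levels and Glial Fibrillary Acidic Protein (GFAP) levels" and "Brain-derived neurotrophic factor (BDNF) and Neurogranin levels by using commercially available arrays". Connectivity comes from resting-state and diffusion MRI.

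The purpose is set out in Section 1.2: "we aim to evaluate the changes in brain activity and molecular markers as they relate to the intervention". Of the trial as a whole, the same section says: "It will increase understanding of the neural and biological characteristics linked to the effect of language treatment and non-invasive brain stimulation application in PPA".

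Section 2.8 also plans a repeated-measures comparison of the two groups over time, and repeated-measures ANOVAs for the MRI data. The factors listed for those ANOVAs are time, hemisphere and electrode site.

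**The concern.** The mechanistic question is whether patients whose marker changes more also improve more, beyond the fact that both changes may follow from receiving active stimulation. A bivariate coefficient over all patients mixes two sources of covariance: the association among patients within an arm, and the difference between the arm means. If treatment shifts both variables, the second source alone produces a correlation. Its sign is that of the product of the two arm effects, and its size says nothing about a patient-level link.

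The between-group comparisons in Section 2.8 do not fill this gap. They can show that a marker or a score moves with allocation, but not that the two move together in patients. What is at stake is the reading of the mechanistic results: a marker could be reported as tracking benefit when it only responds to the same allocation.

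**Working it through.** **The plan's own figure.** The article gives no figure for the correlations. Its only related number is the minimum of 12 subjects in Section 2.2 (eta square 0.25, 90% power, alpha 0.05).
- f = sqrt(0.25 / 0.75) = 0.577.
- The time-by-group interaction with two groups, two time points and an assumed correlation of 0.5 between repeated measures gives N = 12 (power 0.949). Three time points give N = 10 (power 0.961).

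The figure of 12 therefore reproduces under common defaults, and the effect size can be carried forward.

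**Inputs**
- Arm effect on naming change: eta square 0.25 read as a 1:1 two-arm contrast, so d1 = 2 × 0.577 = 1.155 within-arm SD. This reading is an assumption.
- Arm effect on the marker change, d2: not in the document. Assumed range 0.3 to 1.155 SD.
- Sample: 60 randomised; with the 20% dropout of Section 2.2, 60 × 0.8 = 48.
- Within-arm correlation: zero, so there is no patient-level link.

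**Pooled correlation**

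r = (d1·d2/4) / sqrt[(1 + d1²/4)(1 + d2²/4)]

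- d1 = 1.155, d2 = 0.5: 0.144 / sqrt(1.333 × 1.0625) = 0.12
- d1 = 1.155, d2 = 0.8: 0.231 / sqrt(1.333 × 1.16) = 0.19
- d1 = d2 = 1.155: 0.333 / 1.333 = 0.25

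**Rejection rate of the two-sided 5% test** (20,000 simulated trials per row, normal data, equal arms)

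| Arm effects (SD): naming or score, marker | Pooled r | Plain Pearson, n = 48 | Plain Pearson, n = 60 |
|---|---|---|---|
| 1.155, 0 | 0 | 4.9% | 5.0% |
| 0.3, 0.3 | 0.02 | 5.1% | 5.0% |
| 0.5, 0.5 | 0.06 | 6.7% | 7.0% |
| 0.8, 0.8 | 0.14 | 15.7% | 18.6% |
| 1.155, 0.5 | 0.12 | 12.8% | 15.4% |
| 1.155, 0.8 | 0.19 | 25.3% | 30.3% |
| 1.155, 1.155 | 0.25 | 42.3% | 50.9% |

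With the arm means removed (partial correlation given arm, n − 3 degrees of freedom), the rate is 5.0% at n = 48 and 4.8% at n = 60 in every row. In the rows with arm effects on both variables, the plain rate tends to rise with n, because the pooled correlation is a fixed non-zero quantity; a larger sample does not cure it.

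**The case against.** The strongest reply is that pooling is never stated. A journal article condenses the full protocol, and a Pearson coefficient computed within each arm would satisfy the sentence and be free of the artefact. This stands as a limit: the point is conditional on pooling. It does not remove the point, because the sentence names the estimator and, followed literally across all patients, gives the pooled coefficient.

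Second, the larger rates need sizeable arm effects on both variables. The 1.155 SD is a planning value for naming only, and nothing in the document supports an effect of that size on a plasma or imaging marker. This also stands. At 0.5 SD on both the inflation is slight. Section 2.8 could moreover be read as using marker levels rather than changes; baseline levels are not shifted by treatment and would fall under the no-inflation case. Section 2.6.3, however, defines the surrogate measures as changes.

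Third, correlation is not the only marker analysis, and the trial is a pilot. That is correct, and it limits the weight of the point.

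A reader might go further and infer that several hundred unadjusted correlations are planned. Counting every listed secondary sub-score against the six plasma measures gives 75 × 6 = 450; one score per instrument or subtest gives 28 × 6 = 168. The document does not say that every score is crossed with every marker, and its silence on multiplicity is not a statement that none will be handled, since that is commonly left to the analysis plan. No finding is made on this.

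**Conclusion.** The point holds in conditional form. The one association method that the article fixes cannot separate a patient-level link from a shared response to allocation if the arms are pooled, and separating them is what the mechanistic aim in Section 1.2 needs. Under pooling, zero within-arm correlation, 1.155 SD on naming and an assumed 0.5 to 1.155 SD on the marker, about 13% to 42% of tests are significant with 48 completers (15% to 51% with 60) instead of 5%. The rate is about 7% at 0.5 SD on both, and nominal if only one variable responds.

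It would be too strong to say that unrelated changes will look linked in this trial: that depends on pooling and on marker effects that the document does not give. The point concerns the interpretation of supporting analyses in a pilot. The primary outcome and the sample size are untouched.

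**What to change.** Replace the correlation sentence in Section 2.8 with wording to this effect:

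> Associations between change in naming accuracy (and other cognitive or functional changes) and change in imaging or molecular markers will be estimated by partial correlation given treatment arm, or equivalently by regressing the outcome change on the marker change with arm as a covariate. Skewed concentrations will be analysed on the log scale. These associations are exploratory.

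A coded arm label is enough for this, so the masking of the statistician described in Section 2.3 can be kept. An arm-by-marker interaction and further covariates (baseline values, PPA variant) are optional; with about 48 completers they would be imprecise, and the arm term alone removes the problem shown here.

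The cost is one sentence, one degree of freedom and probably fewer nominally significant correlations to report. No new data or patients are needed.
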